#### Secondary outcome measures

Linear mixed models will also be used to determine the effectiveness of the internet-based emotion regulation training with regard to 1) depressive symptoms (CDI-2); 2) anxiety symptoms (SCARED); 3) parent-report depressive and anxiety symptoms (SCARED-P and CDI-P); 4) therapist-report global functioning, symptom severity and improvement (CGAS and CGI); and 5) self-report emotion (dys)regulation (FEEL-KJ and DERS). Generalized linear mixed model analysis will be used to determine the effectiveness of the internet-based emotion regulation training on the presence of a depressive and/or anxiety disorder (MINI (KID)). The aforementioned procedures will be followed for these secondary analyses.

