## Methods

### Design

To determine the effectiveness of adding E-TRAIN to CBT, we will conduct a multicenter two-arm randomized controlled trial (RCT) using a two-arm parallel group design. We aim to include 138 adolescents with a primary diagnosis of depressive and/or anxiety disorder. After completion of baseline assessment (T0), participants will be allocated to either CBT or CBT + E-TRAIN. Follow-up assessments will take place after 3 (T1), 6 (T2: primary outcome), and 12 months (T3) post-baseline assessment. See Fig. 1 for the trial flowchart. All assessments are online questionnaires, which will be completed by multiple informants (adolescents, parents/caregivers, and therapists), except for the Mini (KID) International Neuropsychiatric Interview (MINI version 7.02) [54, 55], which will be assessed in a telephone interview 6 months after baseline. This protocol was written in accordance with the Standard Protocol Items: Recommendations for Interventional Trials (SPIRIT) guideline [56]. This study has been registered in the Netherlands Trial Register (NL9564). The Medical Research Ethics Committees United (MEC-U) in the Netherlands has approved the study protocol.

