### Participants

The target population consists of adolescents who have been referred to a mental health center and have been diagnosed with depressive disorder and/or anxiety disorder. In order to be eligible, a participant must meet all of the following criteria: 1) primary diagnosis of depressive disorder and/or anxiety disorder according to DSM-5 criteria; 2) enrolling for CBT in regular care; 3) aged 13–19 years; 4) at least moderately proficient in Dutch; and 5) regular access to a computer, tablet or mobile phone with internet connection. Participants will be excluded from participation in this study if they display a current psychotic disorder or acute suicidal behavior.

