#### Assessments

After signing informed consent, all participants will be invited to fill in the baseline assessment (T0). Adolescents and their parents will receive an email with a link to the questionnaires. All assessments will be conducted via the internet, using Castor EDC (Castor Electronic Data Capture (2021.2)). Those who have not completed the assessment within five days will receive a reminder via email. After one week, participants who have not completed the assessment will be approached via telephone by a research assistant. If necessary, adolescents will have the opportunity to fill in the baseline assessment in the presence of a research assistant, who can provide guidance. After completing baseline assessment, participants will receive a voucher of 15 euros.

Follow-up assessments will be administered at 3 months, 6 months, and 12 months after baseline. Similar to the procedure for baseline assessments, participants (adolescents and parents/caregivers) who have not completed the assessment after one week will be reminded via email and telephone. After completing follow-up assessments, participants (adolescents and parents) will receive a voucher of 10 euros for each completed T1 assessment, and 15 euros for each completed T2 and T3 assessment. Additionally, after completion of the T2 assessment, a trained research assistant who is blind for treatment condition will contact each adolescent for a short diagnostic interview by phone to determine the presence of depressive and anxiety disorders at 6-month follow-up. The depression and anxiety sections of the MINI (KID) will be used. After completion of the MINI (KID), each participant will receive a voucher of 5 euros. Both the E-TRAIN and the CBT therapist of the adolescent will fill in short questionnaires as well. The CBT therapist will be asked to complete questionnaires at T0, T1, and T2, and the E-TRAIN therapist will fill in a questionnaire after completion of E-TRAIN.

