##### Diagnosis of depression and anxiety

he presence of a current diagnosis of depression and/or anxiety at T2 will be assessed with the MINI (KID) (version 7.02) [55, 56]. The MINI is a structured, clinician-administered diagnostic interview that is widely used to assess the presence of psychiatric disorders based on the Diagnostic and Statistical Manual of Mental Disorders (Fifth edition; DSM-5) and the International Classification of Diseases (Tenth revision; ICD-10). For adolescents aged 13–17, sections A, B, D, E, F, G, H, U of the MINI KID will be administered. For adolescents aged 18 or 19 years, sections A, AY, B, E, D, F, FA, and N of the MINI will be administered. Both the MINI and MINI KID are well-validated, reliable interviews [54, 55, 76].

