##### Global functioning, symptom severity and improvement

To asses global functioning of the adolescents, the CBT-therapist of the adolescent will fill in the Children’s Global Assessment Scale (CGAS) [83]. Adolescents are rated on a scale from 1 (extremely impaired) to 100 (superior functioning). To measure symptom severity and improvement the Clinical Global Impression Scales will be used (CGI) [84]. The CGI-Severity (CGI-S) is a 7-item scale ranging from a score of 1 (not ill) to 7 (requires inpatient care). The CGI-Improvement (CGI-I) is a 7-item scale that compares ratings of severity with previous measures, with scores ranging from 1 (very much improved) to 7 (very much worse). Both the CGAS and the CGI are widely used measures [83, 85].

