### Data analyses

#### Primary outcome measures

Linear mixed models will be used to determine the effectiveness of adding E-TRAIN to CBT in reducing depressive and anxiety symptoms (measured with the RCADS25). A two-level structure will be used (Level 1: repeated measures, Level 2: patients). The overall treatment effect will first be evaluated in a model with condition and the baseline value of the outcome. Second, between-group differences at each time-point will be examined by adding time and the interaction of time and condition to the model. Time will be treated as a categorical variable, represented by dummy variables. Furthermore, as a sensitivity analysis, we will fit a model adjusted for the total number of completed CBT sessions and other potentially relevant confounders. Imputation of missing data will not be necessary because we will use mixed-model analyses, which adequately handles missing values [98]. Analyses will be conducted on the entire randomized sample (i.e. intention to treat) and on the per protocol/treatment completers sample. For the treatment completers sample of the experimental (E-TRAIN) condition, adolescents who completed ≥ 66% of the online sessions (four sessions or more) will be regarded as completers. The aforementioned main analyses will also be conducted separately for those with a primary diagnosis of depressive disorder, and for those with a primary diagnosis of anxiety disorder. Analyses will be conducted using SPSS version 26 + and R version 3.0 + . Statistical significance will be set at α < 0.05.

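### The MINI (KID) diagnosis is measured once, at 6 months, so the repeated-measures mixed model and the reason given for not imputing do not fit this secondary outcome

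*Protocol article*

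**What the plan says.** All places are in the protocol article.

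- **When the diagnosis is measured.** Design singles out the MINI (KID) as the one assessment that is not an online questionnaire, "which will be assessed in a telephone interview 6 months after baseline". Assessments says that "after completion of the T2 assessment, a trained research assistant who is blind for treatment condition will contact each adolescent". The outcome section on diagnosis also places it at T2. No MINI is described at baseline, T1 or T3.
- **Diagnosis at entry.** Participants requires a "primary diagnosis of depressive disorder and/or anxiety disorder according to DSM-5 criteria". Recruitment and consent says that a psychiatrist or registered psychologist establishes it.
- **Model for the diagnosis.** Data analyses, Secondary outcome measures: "Generalized linear mixed model analysis will be used to determine the effectiveness of the internet-based emotion regulation training" on the presence of a disorder. The paragraph ends: "The aforementioned procedures will be followed for these secondary analyses". No exception is made for the diagnosis.
- **What is carried over.** Data analyses, Primary outcome measures sets out repeated measures (level 1) within patients (level 2). The first model has condition and the outcome's baseline value. The second adds categorical time and its interaction with condition. On missing data: "Imputation of missing data will not be necessary because we will use mixed-model analyses, which adequately handles missing values". The main analysis is by intention to treat, on everyone randomised.

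**The concern.** The carried-over procedures presuppose an outcome measured at baseline and at several follow-ups. The diagnosis has one binary value per adolescent. Two things follow.

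First, most of the specified model has nothing to estimate it from. The odds ratio that comes out may depend on how the software treats a variance on which the data are silent.

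Second, a mixed model copes with missing values by using a patient's other measurements of the same outcome. Here there are none, so the stated reason for not imputing does not apply.

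The Randomization section leaves adolescents, parents, therapists and researchers unblinded and blinds only the T2 interviewers. The diagnosis is thus the trial's only outcome with a blinded assessor, and the natural check on a self-reported primary outcome. Its analysis should be one that can be run as written.

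**Working it through.** The article gives no figure for this outcome, so there is none to reproduce. The only planning inputs used are 138 randomised (69 per arm) and the 35% extra inclusion for drop-out, both from Sample size. The diagnosis rates in step 2 and the drop-out mechanism in step 4 are assumptions for illustration.

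**1. Which fixed effects can be estimated?** Write one row per adolescent with a T2 interview. The columns are:
- intercept = 1 for all;
- condition = 0 or 1;
- baseline diagnosis = 1 for all, by eligibility;
- time = 1 for all, since only T2 exists;
- condition × time = condition.

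Three columns equal the intercept or condition, so the matrix has rank 2 of 5. Only the intercept and condition can be estimated.

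**2. Is the patient variance identified?** With one binary value per patient, a random-intercept logistic model with standard deviation s gives arm j the probability p_j = E[expit(b_j + s·Z)], Z standard normal. For any s, b_j can be chosen to match the observed proportion, so the maximised likelihood is the same at every s.

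Assume 26 of 51 diagnosed with CBT alone and 20 of 51 with E-TRAIN:

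| s | maximised log-likelihood | conditional odds ratio |
|---|---|---|
| 0 | −69.496 | 0.62 |
| 0.5 | −69.496 | 0.60 |
| 1 | −69.496 | 0.56 |
| 2 | −69.496 | 0.46 |
| 4 | −69.496 | 0.27 |

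The likelihood is flat while the odds ratio moves from 0.62 to 0.27. The row s = 0 is ordinary logistic regression: (20/31)/(26/25) = 0.62.

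**3. What does not move?** On the same data, with condition as the only term:
- The log-likelihood with a common proportion 46/102 is 46·ln(46/102) + 56·ln(56/102) = −70.210. The likelihood-ratio statistic is 2 × (70.210 − 69.496) = 1.43, p = 0.23, at every s.
- The marginal risk difference is 20/51 − 26/51 = −0.118 at every s.

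**4. What happens to a missing interview?** An adolescent without it has no other MINI value and adds nothing to the likelihood. The analysis is complete-case.
- Size, if interview loss equalled the planning allowance: 138/1.35 = 102 remain; 138 − 102 = 36; 36/138 = 26%.
- Whether this biases the result depends on why interviews are missing. As one assumed case with no true effect, let the log-odds of diagnosis be −0.1 + 1.2 × standardised T1 symptoms in both arms. Let the log-odds of missing be −1.0 in one arm and −1.0 + 0.8 × T1 symptoms in the other. Then 27% and 29% are missing, the observed prevalences are 48.1% and 43.1%, and the complete-case odds ratio is (0.431/0.569)/(0.481/0.519) = 0.82 instead of 1.00. Information at T1 would explain this missingness, but a complete-case model with condition only does not use it.

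**The case against.** The strongest defence is that this is a carry-over sentence in a condensed article. An analyst with one row per patient would see the time and baseline terms drop out and would fit a logistic regression. Software that returns a zero variance gives exactly that. The outcome is secondary, and the repair is a matter of wording. All of this stands and limits the weight of the point. It does not remove it, because the article names the model and makes no exception. A mixed model clustered on site or therapist could be fitted to a single diagnosis, but the level specified is repeated measures within patients.

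A reader might infer more than the documents support:

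- **That the conclusion on this outcome becomes arbitrary.** Step 3 shows otherwise: with condition alone, only the conditional odds ratio depends on the variance. No particular inflation can be stated, since no document says what variance would be returned.
- **That 26% or more will be lost, and without mention.** The 35% is a planning allowance for drop-out, not an expected loss of interviews. Reminders, telephone contact and a separate interview voucher are planned, and nothing suggests that missing interviews would go unreported.
- **That not imputing must give a wrong answer.** A complete-case logistic model is valid if missingness depends only on covariates in the model. The fault is that the reason offered does not apply.
- **That CGI-Improvement has the same defect.** Table 1 lists the CGI at T0, T1 and T2. Improvement can be rated at both T1 and T2, so a mixed model for it is estimable. The choice of baseline covariate is detail that an article may leave to the full plan.

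**Conclusion.** The point holds for the MINI (KID) diagnosis. As specified, the patient variance is not identified, the baseline value is constant and there is no time factor; two of five fixed-effect columns are estimable. The reported conditional odds ratio would rest on an arbitrary variance unless that variance is zero.

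The no-imputation rationale does not carry over. The analysis would cover only adolescents with an interview, contrary to the stated intention-to-treat analysis of everyone randomised. About 26% (36 of 138) would be left out if interview loss equals the planning allowance; the actual loss is unknown.

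The identification result needs no assumption beyond one interview per adolescent. The odds ratios of 0.27 to 0.62 and the biased 0.82 rest on assumed data. This should be corrected before analysis. It is of moderate weight, because the outcome is secondary and the primary RCADS25 analysis is untouched.

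**What to change.** 1. In Data analyses, Secondary outcome measures, replace the generalized linear mixed model for the MINI (KID) with a single-time logistic regression of T2 diagnosis on condition. Adjust for the stratification factors (primary diagnosis, site) and baseline RCADS25. Report a marginal risk difference with the odds ratio.
2. Limit the statement that imputation is unnecessary to the repeatedly measured outcomes.
3. Multiply impute missing T2 diagnoses from the symptom scores already collected (RCADS25, CDI-2 and SCARED, all at T0 to T3 in Table 1). Give the complete-case result as a sensitivity analysis.

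The minimum repair is to name a single-time logistic model and restrict the missing-data sentence. The covariates, marginal contrast and imputation go further, but use only data the trial already gathers. The cost is revised wording and a little more programming, with no new data and no change to the sample size.

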#### Acceptability and feasibility of E-TRAIN in adolescents

To examine the acceptability and feasibility of E-TRAIN in adolescents and therapists, qualitative research methods aimed at analyzing focus groups will be used.

### Data collection and management

Data collection and management will be conducted with use of Castor EDC. Castor EDC complies with all applicable laws and regulations: Good Clinical Practice (GCP), 21 CFR Part 11, EU Annex 11, and the European Data Protection Directive. Castor EDC servers are located in the Netherlands and hosted according to the international information security norm ISO 27001/27002/9001 and in accordance with the Dutch NEN 7510 norm for information security in healthcare. The E-TRAIN module will be available for participants on the online *Jouw Omgeving* platform: a widely used e-mental health platform for youths that meets all technical demands and guidelines with regard to privacy and data security, such as ISO 27001 and NEN 7510.

## Discussion

This paper describes the study protocol of a randomized controlled trial aimed at assessing the effectiveness of the addition of a guided internet-based emotion regulation training (E-TRAIN) to CBT in reducing depressive and anxiety symptoms in adolescents with a depressive or anxiety disorder compared to CBT alone. Given the high prevalence and undesirable effects of anxiety and depressive disorders in adolescents, it is of great importance to improve treatment outcomes of these patients. Dysfunctional emotion regulation appears to be an important target of intervention in adolescents with aforementioned disorders, and adolescence appears to be a critical time period to enhance emotion regulation strategies. To the best of our knowledge, this study is the first to examine the effectiveness of a guided online emotion regulation intervention in adolescents with a depressive or anxiety disorder. We will investigate whether treatment outcome of CBT may be improved by strengthening ER skills in this vulnerable population. Moreover, this study will enhance knowledge on ER and its associated factors in adolescents with depression and anxiety.

Strengths of the current study are its randomized design and the relatively long follow-up period of 12 months. Another strength is the large battery of clinically relevant and validated outcome measures that are administered by multiple informants at multiple assessments. An important concern in the field of e-health research is treatment adherence, since internet-based treatments generally are associated with high dropout levels (e.g., [47]). It is expected that the relatively small amount of E-TRAIN sessions, three video conference sessions and weekly guidance of the therapist will enhance treatment adherence. However, this will remain an important challenge of this trial.

If this study provides evidence for the effectiveness of E-TRAIN, it can be an important addition to mental health care for adolescents with depressive and/or anxiety disorder.

## Data Availability

During the ongoing data collection researchers will only have restricted access to the data. After completion of the study, only the Principal Investigator [name] and the Study Coordinators (JE and MW) will have access to the data. Raw data cannot be made openly accessible to the public, due to privacy concerns. After request to the corresponding author, the data, statistical parameters and statistical code will be made accessible. Results will be published in international peer-reviewed journals and will be presented at scientific conferences. We will also report our results to relevant stakeholders in newsletters and trial summaries. All participants and parents will receive a written summary of the results after completion of the study. The publication of the results will be independent of the results, whether or not the experimental intervention is effective. Eligibility of authorship will be decided according to the guidelines of the International Committee of Medical Journal Editors (ICMJE). In accordance with the national regulations in The Netherlands, data will be stored for 15 years.

## Abbreviations

AUDIT: Alcohol Use Disorders Identification Test
BSI-18: Brief Symptom Inventory – Short version
CBT: Cognitive behavioral therapy
CCNES-A: Coping with Children’s Negative Emotions Scale – Adolescent Version
CDI: Children’s Depression Inventory
CDI-P: Children’s Depression Inventory – Parent version
CGAS: Children’s Global Assessment Scale
CGI: Clinical Global Impression Scales
CSQ-8: Client Satisfaction Questionnaire
DERS: Difficulties in Emotion Regulation Scale
ER: Emotion regulation
FEEL-KJ: Der Fragebogen zur Erhebung der Emotionsregulation bei Kindern und Jugendlichen
IPPA: Inventory of Parent and Peer Attachment
MINI: Mini International Neuropsychiatric Interview
RCADS25: Revised Children’s Anxiety and Depression Scale – Short Version
RSES: Rosenberg Self-Esteem Scale
SCARED: Screen for Child Anxiety Related Disorders
SCARED-P: Screen for Child Anxiety Related Disorders—Parent Version
SRSQ: Sleep Reduction Screening Questionnaire
SUS: System Usability Scale
